**Fig 3 pone.0319020.g003:**
[figure not shown]
Cynnau|Ignite Theory of Change describing inputs, activities and anticipated short-term outcomes. Potential Moderators and Unintended Consequences are outlined in red.

The effectiveness quantitative evaluation (displayed alongside Cynnau|Ignite’s implementation plan in Fig 1) is a prospective evaluation with three assessment moments: within two weeks of the start of the programme (baseline – T1), and two weeks following the final session (short-term follow up – T2), then six months after the end of the programme (mid-term follow up – T3). Fig 4 presents the Participant Flowchart. All cohorts will complete the baseline and short-term follow up, with an additional mid-term follow up for the R-only cohort (as course timetabling allows). A control group of university staff who did not take part in Cynnau|Ignite will fill in the baseline and short-term follow up with a 6-month gap in between, which equals the shorter period of Cynnau|Ignite implementation across the three groups (i.e., for the PST/S group) and is therefore comparable with the baseline and short-term follow up assessments for the cohorts.

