### Participants

The intervention group will consist of all learners, comprised of four cohorts (two T&R cohorts, one R and one PST/S cohort) with 32 learners in each. All those accepted into Cynnau|Ignite will be eligible to take part in the study and will integrate the intervention trainee groups. Selection criteria for Cynnau|Ignite will be those employed at Cardiff University at grade six, seven or eight as Teaching and Research, and Research-only staff, along with Professional Service staff, or Technicians at grades 5 to 8, in any discipline. Applicants will be expected to demonstrate that they have an interest in PRC and are available to attend all sessions, with allowances made for those who are unable to attend a single session. These criteria mirror common practice for similar training programmes at Cardiff University and will be likely to remain unchanged, unless if demand will need to be addressed in future Cynnau|Ignite iterations. We expect high participation and low attrition in the intervention group. No concealment or blinding will be used in this research. All learners will be allocated to either the Teaching and Research, Research-Only, or Professional Services, Technicians and Specialists version depending on their career path.

Inclusion criteria for the control group will be being a Cardiff University employee at grade six, seven, or eight who is not enrolled in the programme. Based on moderate attrition rates between 20–50% [17,18] observed in repeated measures surveys and organizational research, we intend to recruit a total of 96 staff members for this group, with a maximum of 32 participants each from T&R, R and PST/S roles. A power analysis conducted using GPower [19] indicates that this will provide enough power to detect small to moderate effect sizes (repeated measures ANOVA, p = .90, f =  0.15, α = .05) in differences between the learner and control groups in changes in intentions from baseline (T1) to follow up (T2) and in differences between the R and control groups in changes in intentions from baseline (T1) to follow ups (T2 & T3).

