Effectiveness and impact (Research Question 4) will be reported for all learners, but the analytical strategy will depend on the final sample achieved. Cardiff University has a total of 26 academic schools, all of which are eligible for Cynnau|Ignite. To account for non-independence of data we will use multi-level modelling [30] with learners (level 1) nested within schools (level 2), but only if the recommended 20 schools/units are achieved [31]. If this is not possible, we will use two-way Mixed ANOVA. Analysis will investigate how Cynnau|Ignite affects self-reported intentions and actual PRC behaviours (primary outcomes), attitudes, norms and PBC (secondary outcomes), with Group (Cynnau|Ignite, Control) as the between-subject variable and Time (T1, T2) as the within-subject factor. Similar analysis will be used to compare each Cynnau|Ignite group (T&R, R, PST/S) with the control group and to investigate changes in the study outcomes across a 6-month period following Cynnau|Ignite, the latter with Time (T2, T3) as the within subject factor for the R-only cohort. Statistical significance will be indicated if *p* < 0.05 and effect sizes will be reported for all analysis. Finally, we will quantitatively analyse the organisational impact of Cynnau|Ignite by investigating learner and control group differences with multilevel modelling, or Mixed ANOVA if the necessary units are not reached, in perceptions of PRC at Cardiff University. Descriptive and inferential statistics will be used to map the impact of Cynnau|Ignite on impact indicators, such as the implementation of Action Learning projects related to research culture, and learners’ uptake of mandatory staff training compared to those who did not participate in Cynnau|Ignite.

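### The .90 power stated for Research-only versus control through T3 has no matching test, because controls are surveyed only at T1 and T2; for the T1–T2 comparison that can be run, 90% is not assured

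*Protocol article*

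**What the plan says.** Participants gives the power basis as "repeated measures ANOVA, p = .90" (the p is read here as power), with f = 0.15 and α = .05, described as "enough power to detect small to moderate effect sizes". Two comparisons are covered:

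- all learners: "in differences between the learner and control groups in changes in intentions from baseline (T1) to follow up (T2";
- the R cohort: "in differences between the R and control groups in changes in intentions from baseline (T1) to follow ups (T2 & T3".

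The same section describes the learners as "comprised of four cohorts (two T&R cohorts, one R and one PST/S cohort) with 32 learners in each". It sets a control recruitment target of 96 and cites attrition of 20–50% in comparable surveys.

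Under Study design, the control group "will fill in the baseline and short-term follow up with a 6-month gap in between", while all cohorts complete T1 and T2 "with an additional mid-term follow up for the R-only cohort". Table 1 (Outcomes) lists the T2–T3 comparison for R-only learners. Analytical methods plans to compare each programme group with control, and to study the six months after the programme, "the latter with Time (T2, T3) as the within subject factor for the R-only cohort".

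**The concern.** A group-by-time contrast needs both groups at every wave it uses. The power sentence promises one for R versus control up to T3, yet no section provides a T3 survey of controls. A reader of the power statement would expect a controlled, well-powered mid-term comparison. What the design delivers is a before–after change in at most 32 people, with nothing to separate persistence of effect from drift across the university or the sector. T3 is also the only evidence beyond the end of the programme.

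Once T3 is removed, the R-versus-control comparison rests on T1 and T2 with 32 learners. The protocol gives that comparison no power figure of its own, so it needs checking whether .90 carries over.

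**Working it through.** **1. Schedule against claim**

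| Section | Control waves | R waves | R-versus-control contrast at T3? |
|---|---|---|---|
| Participants (power) | implied T1, T2, T3 | T1, T2, T3 | claimed |
| Study design | T1, T2 | T1, T2, T3 | not possible |
| Outcomes, Table 1 | none listed for T3 | T2, T3 | no |
| Analytical methods | T1, T2 | T2, T3 within cohort | no |

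Three sections agree with each other; the power sentence is the one out of line. This step needs no assumption.

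**2. Inputs**

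From the protocol: f = 0.15, α = .05, power .90, R = 32, all learners 4 × 32 = 128, controls 96. After 20% attrition, 96 × 0.8 = 76.8, about 77 controls; after 50%, 48. Learner attrition is described as low without a figure and is taken as zero. The within-person correlation ρ is not stated, so .5 is assumed, with a range of .3 to .7.

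**3. Formula**

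G*Power within–between interaction, noncentral F, sphericity assumed:

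λ = f²·N·m/(1 − ρ), df1 = (k − 1)(m − 1), df2 = (N − k)(m − 1), with k = 2 groups and m waves.

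Unequal groups can be handled in two ways, and both are shown:

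- (A) f entered on total N;
- (B) the mean difference held fixed, with N in λ replaced by 4·n1·n2/(n1 + n2).

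**4. Reproducing .90**

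With m = 3 and ρ = .5, N = 96 gives λ = 0.0225 × 96 × 3/0.5 = 12.96 and power .90. The figure therefore reproduces if both groups have three waves and the *total* is 96. In the protocol, 96 is the number of controls, so the match is suggestive only, and it depends on ρ. With m = 2, 90% needs N = 119 (120 with equal groups).

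**5. All learners versus control, T1–T2, ρ = .5**

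- 128 v 96: .99 (A and B).
- 128 v 48: .98 (A), .94 (B).

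This claim is supported.

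**6. R (32) versus control, T1–T2**

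Example with 77 controls and ρ = .5:

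- (A) λ = 0.0225 × 109 × 2/0.5 = 9.81, power .87.
- (B) 4 × 32 × 77/109 = 90.4, λ = 0.0225 × 90.4 × 2/0.5 = 8.14, power .81.

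| Controls | ρ = .3 (A / B) | ρ = .5 (A / B) | ρ = .7 (A / B) |
|---|---|---|---|
| 96 (no attrition) | .81 / .69 | .92 / .83 | .99 / .97 |
| 77 (20%) | .75 / .67 | .87 / .81 | .98 / .95 |
| 48 (50%) | .61 / .59 | .755 / .74 | .93 / .92 |

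The lowest ρ that gives 90% with 96, 77 and 48 controls is .47, .55 and .67 under (A), and .60, .62 and .68 under (B).

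**The case against.** The strongest reply is that only one clause is wrong. Study design, Table 1 and Analytical methods agree, and the main comparison, all learners versus control at T1–T2, is adequately powered. That stands, and it limits the point to the R-versus-control sentence.

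Three stronger readings are tempting, and the protocol supports none of them.

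- **That R versus control at T1–T2 simply falls short of 90%.** This depends on ρ and attrition. With all 96 controls, ρ = .5 and f on total N, power is 92%; at ρ = .7 it is at least 92% throughout. Nor can 32 be set against the equal-group requirement (60 per group for two waves, 48 for three), because the groups are 32 and 96. Three waves at 32 v 96 and ρ = .5 would give .90 even under (B), had controls been surveyed at T3.
- **That T2–T3 within R has 38% power against a promised 90%.** The protocol makes no power claim for that test. The 38% (n = 32, ρ = .5) is for a 0.3 SD change in one group (2f), whereas f = 0.15 in the two-group, two-wave interaction is a 0.6 SD difference in changes (4f). A 0.6 SD change in one group of 32 would have about 91% power.
- **That a non-significant T2–T3 change will be reported as maintenance.** The protocol does not say so, and it plans effect sizes for every analysis. The Discussion also concedes the six-month horizon and the difficulty of separating programme impact from wider change with an unmatched control group. It does not mention that there is no control at T3, so a caution about interpretation is still worthwhile.

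**Conclusion.** The contradiction is firm and rests on no assumption: the .90 for R versus control through T3 has no matching data or analysis. The consequence for T1–T2 is conditional. With 32 R learners, no learner loss and 77 to 48 retained controls, power is about 74–87% at ρ = .5, 59–75% at ρ = .3 and 92–98% at ρ = .7. Whether .90 is reached therefore turns on a correlation the protocol does not give. The all-learners claim at T1–T2 is not in question at ρ = .5.

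**What to change.** 1. In Participants, delete T3 from the R-versus-control power sentence so that it agrees with Study design, Table 1 and Analytical methods.
2. State the within-person correlation and the completers assumed in each group, and restate the R-versus-control T1–T2 power (about 74–87% if ρ = .5 after the stated attrition).
3. In Analytical methods, label the R cohort's T2–T3 analysis as an uncontrolled within-group estimate. Report it with confidence intervals, and say that p > 0.05 will not be taken as evidence that effects were maintained.

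The cost is wording and a less favourable stated power for the R comparison.

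A T3 survey of controls is optional and would be only a partial remedy. T3 would fall about 12 months after a control's baseline (six to T2, six more to T3). With project completion given as 01/02/26 under Confidentiality, it could cover only controls with a baseline by about early 2025 or before, and those at the limit would leave no time for analysis. Control recruitment runs to 1 July 2025, so later recruits would be missed. The change would also need an ethics amendment.

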### Recruitment

The Cynnau|Ignite programme brochure will inform staff they will be invited to participate in this evaluation study. Staff who apply and are selected for the programme will receive an invitation to participate in the research in their Welcome Pack. In the event Cynnau|Ignite exceeds recruitment targets eligible participants will be chosen to maximise representation across roles, schools and units, however if this is not possible, participants will be randomly selected. As such, recruitment for the Cynnau|Ignite participant group will begin on 1^st^ September 2024, and end 8^th^ January 2025 (dependant on cohort start date). Recruitment for the control group will begin 1^st^ September 2024 and run until 1^st^ July 2025 or until target numbers have been reached and will first target staff who indicates an interest in attending Cynnau|Ignite (e.g., request brochure) but do not apply or are not selected, via email invitation. If recruitment targets are not reached with this strategy, participants will be recruited more widely within the university using CU communication channels. All non-trainee participants (e.g., heads of schools) will be invited to participate via email.

All prospective participants will be signposted to the Participant Information Sheet and Consent Form, where they will be required to provide full written informed consent before taking part in this research. After providing consent, participants will be directed to the baseline survey.

### Materials

Data collection materials are outlined below. For a detailed description, please see the ‘Cynnau|Ignite Evaluation Materials Table’ (S2 in supplementary materials), and the materials will be deposited in the UK Data Service repository at the end of the study (https://ukdataservice.ac.uk). All surveys in this study will be presented on Qualtrics (https://www.qualtrics.com). The quantitative evaluation, including the baseline (T1), and follow up (T2, T3) surveys will collect the following data:

Participants’ background (e.g., gender, ethnicity) and professional status (e.g., career path, type of contract).Participants’ attitudes, subjective norms, PBC, intentions, and actual behaviour relative to PRC practices, organised according to the 6 dimensions of the UKRI PRC framework [4] that are targeted by Cynnau|Ignite (research integrity, open approach to research, communicating research, ensuring inclusive work environments, building collegiality, and realising impact) and evaluated with questions developed specifically for the study following the guidelines provided in the TPB manual [20].Research skills targeted by Cynnau|Ignite, with bespoke questions around creativity, leadership, and career development mapped to domains of the UKRI PRC Framework [4].Experiences at work, including participants’ perceptions of a workplace community of practice (as defined by Harvard Business Review) [21], workload, and job satisfaction [22].For the follow up surveys only: One closed and one open question about uptake of other PRC initiatives or training during the Ignite|Cynnau training period, created for this study to mitigate the risk of other PRC initiatives impacting these results.

In addition to the primary quantitative evaluation surveys, short stream evaluations will take place during the last module of each stream. Learners will fill in short evaluation forms, approximately five minutes in length, presented on Qualtrics. Adapted from Rowbottom et al. [23] these consist of five-point Likert scales asking learners to reflect on their experiences throughout the stream, for example whether they found the content appropriate, useful, or boring.

Structured observations will also be used to investigate learners’ engagement with, and reactions to, the programme content. A total of 12 half-day Cynnau|Ignite sessions, split between am and pm sessions, were randomly selected for observation (approximately three per cohort). Using a modified version of Lane and Harris’ Tool for Measuring Student Behavioural Engagement [24] which we tailored to ensure the tool sufficiently captured the behaviour of university staff in an active-learning programme, we will note the number of learners exhibiting specific behaviours such as reading, writing, and making eye contact with the facilitator, at ten-minute intervals throughout observation sessions. This data will be noted anonymously, and at group level, along with narrative annotations where necessary for context.

Process evaluation data will be collected via semi-structured interviews and based on realist principles [25,26]. We aim to collect participants’ views about the outputs (positive, negative) triggered by Cynnau|Ignite and how (theory of change), for whom, and under which circumstances these are triggered [27,28]. Finally, impact evaluation data will be collected via desk review and the above-mentioned interviews, and overall perceptions of PRC at Cardiff University will be measured in the biennial Research Culture Survey. (https://www.cardiff.ac.uk/documents/2741029-research-culture-survey-report-2023-executive-summary), and compared between the intervention and control groups.

### Analytical methods

Mixed methods analysis will be carried out, using SPSS and NVivo for quantitative and qualitative analysis respectively. Descriptive (n, proportions) and inferential (ANOVA, Chi-Square) statistics will be used to describe participants’ background and professional characteristics. Research Questions 1–3 will be investigated using semi-structured interviews, as part of a process evaluation based on realist principles [24,25], which will cover the topics described in Table 1 using an explanatory sequential mixed methods design. Here, data monitoring, session observations and short stream evaluations (completed by learners at the end of each Cynnau|Ignite stream) will be quantitatively analysed using descriptive (n, proportions) and inferential (ANOVA, Chi-Square) statistics; these results will help to inform part of the process evaluation and subsequent qualitative analysis of semi-structured interviews. Content analysis with hybrid deductive and inductive coding [29] will be used to create an iterative framework based on existing literature, and any relevant data from our acceptability or effectiveness analysis. Due to the subjective nature of qualitative data analysis, we will take additional steps to ensure rigour and authenticity in these elements of our research including use of multiple data coders. At regular intervals, coders will be engaged, debriefed and encouraged to reflect on how their own biases may impact the analysis.

Effectiveness and impact (Research Question 4) will be reported for all learners, but the analytical strategy will depend on the final sample achieved. Cardiff University has a total of 26 academic schools, all of which are eligible for Cynnau|Ignite. To account for non-independence of data we will use multi-level modelling [30] with learners (level 1) nested within schools (level 2), but only if the recommended 20 schools/units are achieved [31]. If this is not possible, we will use two-way Mixed ANOVA. Analysis will investigate how Cynnau|Ignite affects self-reported intentions and actual PRC behaviours (primary outcomes), attitudes, norms and PBC (secondary outcomes), with Group (Cynnau|Ignite, Control) as the between-subject variable and Time (T1, T2) as the within-subject factor. Similar analysis will be used to compare each Cynnau|Ignite group (T&R, R, PST/S) with the control group and to investigate changes in the study outcomes across a 6-month period following Cynnau|Ignite, the latter with Time (T2, T3) as the within subject factor for the R-only cohort. Statistical significance will be indicated if *p* < 0.05 and effect sizes will be reported for all analysis. Finally, we will quantitatively analyse the organisational impact of Cynnau|Ignite by investigating learner and control group differences with multilevel modelling, or Mixed ANOVA if the necessary units are not reached, in perceptions of PRC at Cardiff University. Descriptive and inferential statistics will be used to map the impact of Cynnau|Ignite on impact indicators, such as the implementation of Action Learning projects related to research culture, and learners’ uptake of mandatory staff training compared to those who did not participate in Cynnau|Ignite.

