**Fig 1 pone.0319020.g001:**
[figure not shown]
Schematic chronologic representation of Cynnau |Ignite’s implementation and evaluation.

Three versions of the programme will be delivered, tailored to the career needs of Early Career Researchers (ECRs) on Teaching and Research (**T&R**: 2 cohorts of 32 learners), or Research-only (**R**: 1 cohort of 32 learners) career pathways, as well as Professional Services colleagues, including Technicians and Specialists (**PST/S**: 1 cohort of 32 learners) across all disciplines in the university. Details of each tailored programme can be seen in Fig 1.

Fig 2 presents Cynnau|Ignite’s streams, modules, and sessions as mapped against the dimensions of the UKRI PRC framework that are targeted by the programme. Module Learning Outcomes can be found in supplementary material.

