**Fig 2 pone.0319020.g002:**
[figure not shown]
Cynnau|Ignite streams and modules, mapped against relevant dimensions of the UKRI Research Culture Framework.

The programme’s tailored training sessions are hypothesized to help learners promote positive values and attitudes towards PRC, develop a relevant skill set (research career development, leadership) leading to higher perceived efficacy in enacting PRC, and aid in the creation of a community of practice that normalises PRC. In turn, according to the Theory of Planned Behaviour these elements should lead to the creation of strong intentions to practice, and advocate for, PRC and its subsequent behavioural enaction, which is supported by the Action Learning stream of the programme. Learners’ enaction of PRC practices is also expected to lead to improvements in stakeholders’ perceptions of, and in organisational indicators of, PRC at Cardiff University.

Cynnau|Ignite will be run as an interactive programme and all members of the delivery team have experience with participant engagement and a background in designing and implementing training programs for leadership, research skills and/or culture. Except for the Influencing Change module, all content was designed by a network of internal Cardiff University specialists aided by contributors such as specialists or Heads of School, who have specific knowledge and skills pertaining to the session they have been asked to lead. However, Influencing Change will be delivered by an external provider, 64 Million Artists, due to their expertise in creative leadership and helping academics to raise their research ambitions and shape thriving university environments. This provider was able to take a part of their existing “Leading Researchers” programme and create bespoke content to meet the requirements of Cynnau|Ignite’s Influencing Change learning outcomes. Discussions between both parties demonstrated similarities in leadership ethos and partnering expectations, for example, enthusiasm about creativity, belonging, and meaningful connections. Compared to other external providers, 64 Million Artists were able to provide additional strengths mapping opportunities, as well as make all session dates within the budget expected.

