The programme will primarily be delivered face-to-face, however online access will be provided if it is requested as a reasonable adjustment due to personal circumstances (considered on a case-by-case basis). All training sessions will be held in conference rooms, either within Cardiff University or at an external venue, and rooms will be large enough to accommodate 32 participants and several members of the delivery team. Each session will run from 9 am until 4.30 pm, inclusive of lunch and rest breaks, and all learners must commit to attend all modules during the application process, with some flexibility given for those who cannot attend a single date. Attendance will be monitored and recorded.

Throughout, learners will have access to a physical Cynnau|Ignite workbook, featuring materials which guide them through all individual and group activities for each module (e.g., values and self-leadership assessments), and an online Microsoft Teams channel, where learners will have on-demand access to PowerPoint slides summarizing each module, and related reading materials. Using this channel, learners will have the ability to interact with programme facilitators and others in their cohort and share PRC resources. Learners are not restricted from engaging in other PRC initiatives or training programmes on their own volition, both within and outside Cardiff University.

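### The analysis allows for clustering by school at most and leaves out the training cohort, so intervals are too narrow for conclusions beyond these four deliveries, and R and PST/S each rest on one delivery

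*Protocol article*

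**What the plan says.** Analytical methods sets out to deal with dependent observations through "multi-level modelling [30] with learners (level 1) nested within schools (level 2". This model is used only if at least 20 schools or units are represented. Otherwise a two-way Mixed ANOVA of Group by Time is used, which carries no cluster term. The same approach compares T&R, R and PST/S each with control, with significance at p < 0.05.

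Participants describes the intervention arm as "comprised of four cohorts (two T&R cohorts, one R and one PST/S cohort) with 32 learners in each". The Cynnau|ignite programme section gives T&R "2 cohorts of 32 learners", and R and PST/S "1 cohort of 32 learners" each. That section also shows that a cohort is taught as a group:

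- Delivery is mainly face-to-face, and "rooms will be large enough to accommodate 32 participants and several members of the delivery team".
- On the Teams channel, "learners will have the ability to interact with programme facilitators and others in their cohort".
- The training is expected to "aid in the creation of a community of practice that normalises PRC".

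Cohorts are defined by career pathway and are open to any discipline. Under Recruitment, oversubscription is handled by spreading places over roles, schools and units. Cohorts therefore cut across schools. The limitations in the Discussion mention unequal training content, the unmatched control group and wider sector change. They do not mention clustering by cohort or the single delivery of two versions.

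**The concern.** People who spend full days together, work through group activities and are encouraged to form a common norm will tend to change together. If one cohort gels or falls flat, its 32 members shift jointly. A model with school as its only grouping, or with none, reads that shift as 32 separate pieces of evidence. Controls have no matching structure, so the omission affects one arm only.

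Two things are at stake. For the pooled comparison, the interval understates uncertainty about what another run of the programme would achieve, and the Discussion wants lessons for other institutions. For R and PST/S, the planned comparison with control is labelled as the effect of a version but is observed in one group at one time. The Discussion says that recruitment takes place at different times for each group, so calendar timing is tied to version as well. The T2 to T3 analysis uses the same single R cohort.

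**Working it through.** **1. The plan's own figure.** Participants states power 0.90 for f = 0.15 at α = 0.05 with 96 controls. For the repeated-measures interaction, λ = f² × N × m / (1 − ρ), where m is the number of time points. The article does not give ρ. At an assumed ρ = 0.5, two groups and two times need N = 119, and two groups and three times need N = 96. The planned 128 + 96 = 224 gives λ = 0.0225 × 224 × 2 / 0.5 = 20.16 and power 0.994. The statement reproduces for the pooled comparison if all learners are independent. (At ρ = 0.3 the two-time requirement is 166; at ρ = 0.7 it is 73.)

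**2. Inputs for the cohort check.** Cohort size is 32 and there are four cohorts, so 4 × 32 = 128 learners, against 96 controls (all from Participants). The cohort ICC of change is not in the article, so 0.01, 0.05 and 0.10 are assumed.

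**3. Formulas.** The learner arm is clustered and the control arm is not.

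- Design effect: DEFF = 1 + 31 × ICC
- Standard error ratio (true to naive): √[(DEFF/n₁ + 1/n₀) / (1/n₁ + 1/n₀)]
- Actual two-sided error: 2 × [1 − Φ(1.96 / ratio)]

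Example, pooled at ICC 0.05: DEFF = 2.55. The ratio is √[(2.55/128 + 1/96) / (1/128 + 1/96)] = √(0.03034 / 0.01823) = 1.29. Then 1.96 / 1.29 = 1.52, which gives 12.9%.

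| Assumed ICC | 0.01 | 0.05 | 0.10 |
|---|---|---|---|
| DEFF | 1.31 | 2.55 | 4.10 |
| 128 learners are worth (128/DEFF) | 98 | 50 | 31 |
| SE ratio, 128 v 96 | 1.06 | 1.29 | 1.53 |
| Actual error, 128 v 96 | 6.6% | 12.9% | 19.9% |
| Actual error, 128 v 48 (50% control attrition) | 6.0% | 10.0% | 14.9% |
| Actual error, one cohort of 32 v 96 | 7.7% | 18.3% | 28.2% |

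**4. Does the school level absorb this?** A simulation used 1,500 runs per setting, 26 schools, an assumed school share of variance of 0.02, cohorts cutting across schools, and analysis by a school random-intercept model. With four cohorts it rejected a true null in 5.3% of runs at cohort ICC 0, and in 8.8%, 12.1% and 20.5% at 0.02, 0.05 and 0.10. With one cohort the figures were 6.1%, 10.6%, 17.3% and 27.4%. School does not stand in for cohort.

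**5. Power with cohort as the unit.** At ρ = 0.5, f = 0.15 corresponds to 0.6 SD of change. Pooled power with 96 controls (Satterthwaite degrees of freedom) is 0.97, 0.84 and 0.66 at ICC 0.01, 0.05 and 0.10.

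**6. R and PST/S.** One cohort leaves 1 − 1 = 0 degrees of freedom between cohorts. No cohort-adjusted standard error can be estimated from the data.

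**The case against.** Several stronger readings are tempting, and the article does not support them.

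- **School is the wrong unit.** It is not. Colleagues and line managers are named as sources of norms, so school is a sensible level in both arms. It is incomplete.
- **Facilitators differ between cohorts.** Nothing says so. The same internal specialists and external provider may teach all four. The documented sources of dependence are the shared sessions, interaction within the cohort, the intended common norm and timing.
- **The intervals are wrong for any purpose.** If the target is the effect of these four deliveries at one university in the pilot year, treating cohorts as fixed is defensible. The error rates above apply to inference beyond them. They assume cohort effects that vary around a mean of zero. If the programme changed nobody, only differences in cohort composition or outside events could produce such variation.
- **The inflation is known to be large.** It is not. The ICCs are assumed, and at 0.01 the pooled test runs at 6.6%.
- **The pooled power claim collapses.** It does not at moderate ICC: power is still 0.84 at 0.05.

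It is also fair to say that the R and PST/S estimates are already planned. Session observations and interviews will throw some light on how delivery varied. Selection into an unmatched comparison may be a larger threat than this one. None of this puts cohort into the analysis or separates version from delivery.

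**Conclusion.** The point holds as an omission. The article itself fixes the clustering level, and that level misses the group in which the intervention is delivered; under the fallback there is no clustering at all. For conclusions that reach past these four deliveries, the pooled interval is too narrow by a factor of about 1.06, 1.29 or 1.53 at assumed cohort ICCs of 0.01, 0.05 or 0.10 with full cohorts of 32 and 96 controls. That runs from minor to serious, and the article offers no value with which to choose. The confounding of version with a single delivery for R and PST/S needs no assumption about the ICC. The study remains worth doing; what needs to change is the stated precision and the wording of two results.

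**What to change.** In Analytical methods:

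1. Report the T1 to T2 effect for the two T&R cohorts separately. They are the only replication within a version, and so the only direct look at variation from one delivery to the next. The R and PST/S estimates are already planned.
2. Give the pooled confidence interval as planned and again under assumed cohort ICCs of 0.01, 0.05 and 0.10. Do this whether it comes from the multilevel model or the fallback ANOVA. Inflating the learner-arm variance by 1 + (m − 1) × ICC, with m the analysed cohort size, is enough. Four cohorts are too few to estimate a cohort random effect well.
3. State R and PST/S results as effects of a single delivery, not of the programme version.

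Recruitment and data collection do not change, since cohort membership follows from enrolment. The cost is wider intervals and a narrower claim for R and PST/S. No analysis of these data can recover the version effect for those two groups.
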